Unfortunately, dropout percentages from Internet-based interventions can be high and do not get enough attention [30]. Also in our pilot study, almost half of the patients did not complete the intervention. Ways to increase compliance rates should therefore be considered. However, specific components that are critical in improving compliance are difficult to identify and experimental manipulation of factors likely to increase compliance in e-health trials are scarce [31]. A meta-analysis suggests that use of mobile phones and text-messaging could improve healthcare outcomes and the processes of care [32] and a RCT showed that telephone reminders increased the frequency of visits to the site of a self-help Internet program for depressive symptoms compared to no reminders [33]. Recently, Mohr and colleges [34] investigated the feasibility of a multimodal e-mental health treatment for depressed patients in a pilot study, and suggested that joint effects of Internet and telephone administered support for depression are promising. In order to further increase compliance, we therefore plan to use telephone support in the form of text-messages in addition to the Internet-based intervention. However, whether extra text-messages would enhance compliance rates for Internet-based PST is not known.

The aims of our RCT will therefore be multiple. First, we will examine the effectiveness of an Internet-based PST self-help intervention on the primary outcome measure depressive symptoms in MS patients and on secondary outcome measures related to depression and MS such as quality of life, fatigue and cognitive functioning. If the intervention shows to be effective, predictors of a favorable outcome will be further explored. Finally, we will investigate whether text-messages added to the intervention will be effective to increase compliance rate of Internet-based treatment.

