## Methods

### Study design

The presented study is a RCT in which a 5-week Internet-based self-help PST intervention will be tested versus a waiting list control group. Eligible and consenting patients will be assessed at baseline (T0), within a week after the intervention (T1), at four months (T2) and at ten months follow-up (T3: only the intervention group). The control group will be measured at the same moments in time. Patients in the waiting list condition who still want to participate in the intervention after they completed the four months follow-up assessment are again measured after the intervention (T4), four months later (T5) and at ten months follow-up (T6). Data will be collected by self-report measures administered through the Internet. In addition, a telephone interview at baseline will be carried out by trained research staff.

Randomization takes place at individual level after baseline measurements (T0). We will use block-randomization with variable block sizes. A randomly allocated number of patients who take part in the intervention will receive supportive text-messages on their mobile phones in addition to the intervention. Allocation will be unknown to the investigators and will be performed by an independent researcher using a computerized random digit generator. The study protocol was approved by the Medical Ethics Committee of the VU University Medical Center (VUmc) (registration number 11/047). Written informed consent is obtained from all participants. Figure 1 displays the flowchart of the study design.

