#### Secondary outcome measures

Secondary outcomes will include measures of anxiety, fatigue, cognitive functioning, physical and psychological impact of MS, quality of life, problem solving skills, social support, mastery, satisfaction and compliance rate. The measurement scales mentioned below have shown to be reliable, valid and responsive, and are widely used as an outcome measure in MS research and/or research on psychiatric conditions.

Anxiety will be assessed with the Beck Anxiety Inventory [42] and the subscale of the Hospital Anxiety and Depression Scale [43]. We will use the Fatigue Severity Scale (FSS) [44] and Multiple Sclerosis Neuropsychological Questionnaire (MSNQ) [45] to measure fatigue and cognitive functioning, respectively. In addition, we will use the Multiple Sclerosis Impact Scale (MSIS-29) [46] to assess the physical and psychological impact of MS and the EuroQol quality of life measure comprising a five-part questionnaire (EQ-5D) and a visual analogue self-rating scale (EQ-VAS) [47]. Social support will be measured with the Social Support Inventory [48] which contains questions on details about social support from the four most intimate persons. We will use the Social Problem Solving Inventory-Revised (SPSI-R) to determine individual problem-solving skills [49]. Furthermore, Mastery or locus of control, is measured by an abbreviated version of the Pearlin Mastery Scale [50]. Between follow-ups; psychotherapy and -medication usage will be registered.

With the Client Satisfaction Questionnaire (CSQ-8) [51] we will check whether patients were satisfied with the care they received. The Visual Analogue Scale (VAS) will be assessed to evaluate patients opinions about the intervention as a whole, the website and received support, (via the website and by text-messages if applicable) and additionally explore reasons for drop-out. Feasibility of additional text-messages will further be assessed by compliance rate; data on number of treatment sessions and drop-out will be collected. Table 1 describes the measures used at each assessment point.

**Table 1 T1:** Summary of measures

**Measure**	**T0: Baseline**	**T1: posttreatment**	**T2: 4-months Follow-up**	**T3: 10-months Follow-up**

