### Text-messages

As part of the intervention, a number of patients will receive weekly text-messages on their mobile phones to support them during the intervention with the aim to enhance compliance. Patients will be randomly assigned to the intervention with- or without text-messages. In the latest case, patients will receive four standard text-messages a week. Text-messages will be sent to their mobile phones 1) at the start of a new module, 2) during the week to remind patients to fill in the exercise and mood-chart, 3) when homework is handed in by email, and 4) when feedback is returned by their coach. When homework is not handed in on time, patients will receive a reminder text-message. Patients cannot reply to the text-messages.

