### Analysis

Non-parametric and parametric statistical tests are used to assess differences between the conditions with regard to baseline assessment of all relevant demographic and clinical variables. Missing data will be processed using regression imputation or a conservative Last Observation Carried Forward method (LOCF) (depending on the sort and size of the missing data). Analysis will be based on the intention-to-treat principle. Paired t-tests are used to assess the changes within each condition between pre-treatment and post-treatment. Difference in outcome between the Internet-based intervention and waiting list control group is evaluated by means of mixed model analysis of covariance and baseline differences will be included as a covariate in the analyses. Treatment effect over time will be tested by adding a group*time interaction term into the model. Cohen’s formula will be used to evaluate the magnitude of the effect of the intervention on outcome measures [52]. To calculate clinically significant improvement and recovery we will use the standardized method of Jacobson and Truax [53]. If the intervention shows to be effective, predictors of outcome will be explored by analyses of interaction between patients characteristics and treatment. Data of waiting list patients who decided to participate in the intervention will be analysed separately. Finally, descriptive statistics of compliance rate and satisfaction will be used to explore the feasibility of text-messages as a way to increase compliance rate to Internet-based treatment.

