## Discussion

The described study protocol is designed to investigate the effectiveness of an Internet-based self-help PST intervention for depressive symptoms in MS patients in a RCT. Treatment through Internet offers the possibility to reach a group of underserved MS patients who could experience disease-related barriers to participate in face-to-face counselling. Besides, the self-help aspect of Internet-based treatment could be appealing to a group of patients that already is dependent of professionals in the medical circuit because of their MS. According to our knowledge, the effectiveness of Internet-based treatment for depressive symptoms in MS patients has not been examined yet. Our trial will also shed more light on the applicability of PST in itself for patients who suffer from MS.

In order to conduct a high-quality trial, a multidisciplinary team with various expertises related to MS and depression was involved in the development of the intervention and the study design. Ways to prevent early termination during the intervention were carefully taken into account since high drop-out percentages in e-health interventions are a common phenomenon. Although multimodal e-mental health treatment seems a promising candidate to increase compliance, additional research on this subject is needed [34]. Evaluation of the effectiveness of text-messages in addition to Internet-based treatment seems therefore a valuable aspect of our trial. Nevertheless, it is still unclear whether effectiveness of additional text-messages can be determined as the trial is powered to demonstrate effects of the intervention and not of text-messaging. Further, follow-up assessments to explore Internet-based PST effects on the long-term could be considered another strength of our trial since data on enduring treatment effects for depression in MS are often not available [11].

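### Text-messages are randomised with the aim of learning whether they raise compliance, but the stated analysis is descriptive only, with no between-group difference or confidence interval

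*Protocol article*

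**What the plan says.** **Aim.** The Background closes its list of aims with "we will investigate whether text-messages added to the intervention will be effective to increase compliance rate of Internet-based treatment".

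**Design.** Study design states: "A randomly allocated number of patients who take part in the intervention will receive supportive text-messages on their mobile phones". The Text-messages section repeats it: "Patients will be randomly assigned to the intervention with- or without text-messages". The ratio and the number allocated to messages are not given.

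**Outcome.** Secondary outcome measures lists compliance rate as an outcome. It treats compliance as a measure of the feasibility of the messages and adds that "data on number of treatment sessions and drop-out will be collected".

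**Analysis.** The one between-group model in the Analysis section concerns the main contrast: "Difference in outcome between the Internet-based intervention and waiting list control group is evaluated by means of mixed model analysis of covariance". For the messages, the section says that "descriptive statistics of compliance rate and satisfaction will be used to explore the feasibility of text-messages as a way to increase compliance rate".

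**Discussion.** "Evaluation of the effectiveness of text-messages in addition to Internet-based treatment seems therefore a valuable aspect of our trial". The next sentence adds the caveat that "it is still unclear whether effectiveness of additional text-messages can be determined as the trial is powered to demonstrate effects of the intervention".

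**The concern.** The Background and the Discussion speak of effectiveness, while the Methods speak of feasibility. The second randomisation only makes sense for a comparative question, and it is what makes an unbiased answer possible. The stated analysis does not use it to produce an estimate.

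At stake is how the result will be read. With perhaps 40 to 55 patients per text-message group, two completion rates can differ by 15 points or more through chance alone. Summaries without an interval would let one reader conclude that messages work and another that they do not. The imprecision that the Discussion concedes would not show in the results.

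**Working it through.** **1. The article's own figure.** The only sample size given is for the primary comparison: d = 0.5, two-sided alpha 0.05, power 0.80. The normal formula n = 2(1.960 + 0.842)² / 0.5² gives 62.8, so 63 per group. The t-test version gives 63.8, so 64, as stated. No figure is given for the text-message contrast, so there is none to reproduce.

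**2. Inputs for the text-message contrast.**
- Total to include: 166 (Sample size). Two equal conditions give 166/2 = 83 intervention patients.
- Split within the intervention: not stated. Assumption A is 83/2 = 41.5 per text-message group. Assumption B is three equal arms, 166/3, or about 55 each.
- Completion without messages: not stated. The Background says that almost half of the pilot patients did not finish the intervention, so 50% is assumed, with 55% as a variation.
- Two-sided alpha 0.05, as for the primary comparison.

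**3. Formulas.** For completion proportions p1 and p2, difference δ, mean p̄ and n per group:
- SE = √[p1(1 − p1)/n + p2(1 − p2)/n], and the 95% half-width is 1.96 × SE.
- SE0 = √[2p̄(1 − p̄)/n], and power ≈ Φ[(δ − 1.96 × SE0)/SE].

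**4. Worked case: 50% against 65%, n = 41.5.**
- SE = √[(0.2500 + 0.2275)/41.5] = 0.1073, so the half-width is 1.96 × 0.1073 = 0.210.
- SE0 = √[2 × 0.575 × 0.425/41.5] = 0.1085, so power = Φ[(0.150 − 0.2127)/0.1073] = Φ(−0.584) = 0.28.

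The same case with n = 55: SE = √(0.4775/55) = 0.0932, half-width 0.183. SE0 = √(0.48875/55) = 0.0943, so power = Φ[(0.150 − 0.1848)/0.0932] = Φ(−0.373) = 0.35.

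**5. Results.**

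| Assumption | Power, 10 points | Power, 20 points | Power, 30 points | Gain detectable at 80% power |
|---|---|---|---|---|
| 41.5 per group, base 50% | 0.15 | 0.46 | 0.83 | 29 points |
| 41.5 per group, base 55% | 0.15 | 0.48 | 0.86 | 28 points |
| 55 per group, base 50% | 0.18 | 0.57 | 0.92 | 26 points |
| 55 per group, base 55% | 0.19 | 0.60 | 0.94 | 25 points |

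For 80% power from a base of 50%, a 20-point gain needs 93 per group, a 15-point gain 170 and a 10-point gain 388. For the number of modules completed, treated as a mean, the standardised difference detectable at 80% power is 0.62 with 41.5 per group and 0.54 with 55.

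**6. Reading.** The comparison is feasible but imprecise under every assumption tried. That is a reason to show the interval.

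**The case against.** Much of the case on the other side stands.

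- **The Methods are consistent with each other.** Secondary outcome measures already treats the messages as a feasibility question, and the Analysis section follows it. The mismatch lies between the Background and Discussion on one side and the Methods on the other.
- **The lack of power is disclosed.** The Discussion says plainly that the trial was sized for the intervention. A modest analysis of an unpowered question fits that caveat.
- **An article condenses.** How completion is defined, or how summaries are laid out, may properly sit in a fuller document and is not faulted here. But the article does not leave this analysis open: it names one, and that one falls short of the stated aim.

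Three stronger readings are tempting, and the article supports none of them.

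- A reader might infer that the randomisation will be ignored, or that patients will be grouped by messages received. Such a grouping would be confounded, because some messages are triggered by handing in homework or by failing to. The article proposes no such grouping. It defines the groups by random assignment and states an intention-to-treat principle, so the summaries could well be tabulated by assigned group. It simply does not say so.
- A reader might infer that the choice of analysis is what makes the aim unanswerable. The main obstacle is sample size. An interval would make the imprecision visible but would not remove it.
- A reader might expect a comparison of BDI-II scores by text-message group. The article ties the messages to compliance only, so such a comparison would be a preference.

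**Conclusion.** The point holds in a limited form. The article states an effectiveness aim for text-messages and randomises patients to them, but its named analysis is descriptive and includes no between-group estimate or interval. Under an even split of about 83 patients and about 50% base completion, the interval would be about ±21 points, with about 28% power for a 15-point gain. With 55 per group the figures are about ±18 points and 35%. The split and the base rate are both assumptions. The matter is worth correcting because the data and the randomisation are already in place. It concerns a secondary, admittedly underpowered question and does not affect the comparison with the waiting list.

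**What to change.** In the Analysis section, state that compliance will be compared by assigned text-message group among all patients randomised to the intervention. Report the difference in the proportion completing all five modules and the difference in the number of modules completed, each with a 95% confidence interval and labelled exploratory. Word the aim in the Background as estimating the effect of text-messages on compliance, so that it agrees with the power caveat in the Discussion. Say in advance that the interval is expected to be wide and that a null result will not be taken as absence of effect.

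If only feasibility is intended, rewording the aim would remove the contradiction, but it would leave the randomised contrast without an estimate.

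The cost is one additional exploratory comparison with a wide interval, on session and drop-out data that the trial already plans to collect. No extra patients or assessments are needed.

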## Discussion

The described study protocol is designed to investigate the effectiveness of an Internet-based self-help PST intervention for depressive symptoms in MS patients in a RCT. Treatment through Internet offers the possibility to reach a group of underserved MS patients who could experience disease-related barriers to participate in face-to-face counselling. Besides, the self-help aspect of Internet-based treatment could be appealing to a group of patients that already is dependent of professionals in the medical circuit because of their MS. According to our knowledge, the effectiveness of Internet-based treatment for depressive symptoms in MS patients has not been examined yet. Our trial will also shed more light on the applicability of PST in itself for patients who suffer from MS.

In order to conduct a high-quality trial, a multidisciplinary team with various expertises related to MS and depression was involved in the development of the intervention and the study design. Ways to prevent early termination during the intervention were carefully taken into account since high drop-out percentages in e-health interventions are a common phenomenon. Although multimodal e-mental health treatment seems a promising candidate to increase compliance, additional research on this subject is needed [34]. Evaluation of the effectiveness of text-messages in addition to Internet-based treatment seems therefore a valuable aspect of our trial. Nevertheless, it is still unclear whether effectiveness of additional text-messages can be determined as the trial is powered to demonstrate effects of the intervention and not of text-messaging. Further, follow-up assessments to explore Internet-based PST effects on the long-term could be considered another strength of our trial since data on enduring treatment effects for depression in MS are often not available [11].

The external validity of our study is high because of the low level of exclusion criteria and the use of Internet that enables us to reach and treat a large part of the MS population. It should be noted that Internet-based treatment may not be suitable for MS patients who are not familiar with the Internet, or who suffer from MS related problems such as impaired vision and arm/hand dysfunction. In addition, we will exclude patients with mild depressive complaints (BDI-II < 20). As a consequence, evidence will be lacking whether the intervention could be effective for this group of patients. However, our pilot-study [29] showed that patient with more severe depressive symptoms experienced more benefit from the intervention than patients with fewer depressive complaints. Moreover, patients with fewer depressive symptoms at baseline (<20) were more likely to drop out of treatment and indicated to be less satisfied with the intervention. A meta-analysis [23] supports this finding and suggests that patients with less severe psychological difficulties may be less motivated to receive ongoing help. Driessen and colleagues concluded in their meta-analysis [54] that psychological treatment might even be more efficacious for more severely depressed patients than low severely depressed patients. For these reasons we decided to focus on MS patients with moderate or high depressive complaints.

To conclude, a study protocol to investigate the effectiveness of Internet-based PST for depressive symptoms in MS patients is presented in order to enhance methodological clarity and further research on treatment for depressed MS patients. Internet-based PST offers the possibility to reach and treat many MS patients with depressive symptoms and to improve the quality of care. Our RCT is aimed at contributing to better recognition and adequate treatment of depressive symptoms in MS patients in the future.

